#### Follow-up assessments

Follow-up assessments for all participants are conducted at week 5 (4 weeks post completion of treatment, + 2-week window), 6 and 12 months (±2-week window).

At the 5-week follow-up appointment, any unused trial medication is collected and returned to the Pharmacy for disposal, and the OSTRICH nurse collects the completed symptom diary from the parent/legal guardian.

Completion of the questionnaire booklets and the clinical assessments (for example, audiometry, tympanometry, and otoscopy) are repeated at each of the follow-up clinic appointments. Although the follow-up of participants is continued for 12 months, after the 5 week assessment all participants resume ‘usual care’, and all treatment decisions are made by their parents in consultation with their clinician.

The questionnaire booklets at 6 and 12 months also include healthcare resource usage to assess use of NHS resources, additional medication taken, time off school/nursery and parental time off work.

In the event that participants’ follow-up appointments are missed at the proposed time points, SEWTU coordinate with the trial site staff, and the parent/legal guardian of the participant is contacted by telephone to rearrange the visit as soon as possible. In the event that telephone contact is not successful, visit reminder letters are sent to rearrange the appointment.

If parents/legal guardians are unable or unwilling to attend a follow-up appointment, they are asked if they are willing to complete the questionnaire booklet that would be sent to them in the post. A freepost self-addressed envelope is provided for parents to return their diary, unused medication and/or questionnaire booklet. Alternatively, they will be given the option of answering a brief questionnaire over the telephone, comprising questions extracted from the diary regarding symptoms (for the 5-week follow-up, if not completing/returning the diary) and quality of life (if not completing and returning a questionnaire booklet).

### Analysis

#### Sample size

The sample size calculation is based on demonstrating a change in the rate of resolution of hearing loss at 5 weeks post randomisation (4 weeks post completion of treatment) from 20 % in the control group to 35 % in the intervention group. OME resolves spontaneously in a high proportion of children, and some studies have found a significantly higher rate of spontaneous resolution. For example, Williamson et al. found a resolution rate in their control group of 47 % [16]. However, we anticipate a lower spontaneous rate of resolution because we will only include children who have been symptomatic for at least 3 months and are recruiting children in a secondary care setting, where a more severe spectrum of illness can be anticipated. The Cochrane review of steroids for OME reported a ratio of proportions for resolution of OME at 2 weeks of 3.80 (95 % CI = 0.93 to 15.52). In the five studies in the Cochrane review of oral steroids versus placebo, overall there was a 23 % recovery rate in the placebo plus antibiotic group and a 47 % recovery rate in the oral steroid plus antibiotic group, which represents a 24 % difference (antibiotics on their own are ineffective) [12]. We have selected a conservative estimate of 1.75 for our effect size (ratio of proportions) because we believe that a 15 % absolute increase in the rate of resolution at 5 weeks would represent a clinically meaningful benefit that could result in a meaningful reduction in unnecessary operations and a related saving in cost for the NHS. In order to demonstrate a difference between 20 % and 35 % with an alpha of 0.05 and 80 % power, we will need 302 participants (nQuery software version 4.0). We will recruit 380 to allow for a 20 % loss to follow-up at 1 year. Although our primary outcome data will be gathered at 5 weeks, we believe that it is important to be able to assess long-term outcomes and, therefore, want to ensure that we will have sufficient power for longer term follow-up assessments.

#### Statistical analysis

The primary analyses will be intention to treat and will employ a logistic regression model to investigate differences in the proportion of children with acceptable hearing at the 5 weeks post randomisation follow-up appointment between the two treatment arms, adjusting for site. Comparisons will be presented as the absolute difference in proportions and the adjusted odds ratio, with 95 % confidence interval and *P* value.

Secondary outcomes with a binary outcome (present/absent), such as satisfactory hearing and presence of effusion, will employ repeated measures logistic regression to investigate differences between the trial arms and over time (5 weeks and 6-month and 12-month follow-ups). Changes in hearing over time will also be analysed to identify children who show early resolution but then relapse. For continuous secondary outcomes, such as PedsQL, and OM8-30 scores, repeated measures linear regression models (using transformations as necessary) will be used to investigate differences between the trial arms and over time (5 weeks, 6 months and 12 months) adjusting for baseline. The duration between the start and the resolution of the symptoms will be calculated and the median (interquartile range) for each randomised group will be presented. A Cox regression model will be used to test whether time to resolution differs between the randomised groups.

A number of outcomes will be calculated from the parents’ diary for the first 5 weeks, such as total time off school/nursery and work (days) and the number of healthcare consultations. These will be analysed using Poisson regression to investigate differences between the two trial arms.

Previous researchers have mapped OM8-30 scores to utility values on the HUI-3 scale. As this trial measures both OM8-30 and HUI-3, it provides the opportunity to evaluate the generalisability of the existing mapping. This will be done by correlating the mapped utility values on the HUI-3 scale (obtained via the mapping formula from the OM8-30 facet scores) with the newly acquired HUI-3 scores.

Possible confounders such as the child’s age and history of atopy and relevant interaction terms will be entered into the primary regression analyses for each of the outcomes in order to conduct pre-specified subgroup analyses. These subgroups will be defined in advance of any analysis based on the best available evidence. Since the trial is powered to detect overall differences between the groups rather than interactions of this kind, the results of these exploratory analyses will be presented using confidence intervals as well as *P* values. No interim analyses are planned.

Full description of the methods to be used will be stated in a trial statistical analysis plan.

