### Inclusion criteria

The inclusion criteria are as follows:Age 2 to 8 years (for example, has reached the 2^nd^ birthday and has not yet reached the 9^th^ birthday).Symptoms of hearing loss attributable to OME for at least 3 months (or had audiometry proven hearing loss for at least 3 months).Diagnosis of bilateral OME made in an ENT or Paediatric Audiology and AVM clinic on the day of recruitment or during the preceding week.Audiometry confirming hearing loss of more than 20 dBHL averaged within the frequencies of 0.5, 1, 2, and 4 KHz in both ears by pure tone audiometry (PTA) ear-specific insert, visual reinforcement audiometry (VRA) or ear specific play audiometry, or hearing loss of more than 25 dBHL averaged within the frequencies of 0.5, 1, 2, and 4 KHz by sound-field VRA or sound-field performance/play audiometry in the better hearing ear, on the day of recruitment or within the preceding 14 days.First time in the OSTRICH trial.Parent/carer able to understand and give informed consent.

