### Outcomes

The primary outcome is acceptable hearing at 5 weeks from randomisation (4 weeks after conclusion of treatment), where acceptable hearing is defined as ‘less than or equal to 20 decibel hearing level (dBHL)’ averaged within the frequencies of 0.5, 1, 2 and 4 kilohertz (kHz) in at least one ear in children assessed by pure tone audiometry (PTA), ear-specific insert visual reinforcement audiometry (VRA) or ear-specific play audiometry, and ‘less than or equal to 25 dBHL’ averaged within the frequencies of 0.5, 1, 2 and 4 KHz in children assessed by sound-field VRA or sound-field performance/play audiometry. These thresholds are based on national guidelines [25].

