#### Registration and consent

Participating clinicians (ENT or Audiovestibular Medicine) identify eligible patients with bilateral hearing loss and diagnosis of OME during routine outpatient consultations, from current grommet surgery waiting lists or from hearing aid review lists. Additionally, potentially eligible children are identified in Audiology, Audiovestibular (AVM), Paediatric Audiology and Community Audiology clinics, and interested parents/legal guardians will be directed to the participating OSTRICH clinician.

Each child has an audiometry assessment and a clinical assessment (both routine procedures for those attending these clinics) before they are assessed for eligibility to enter the trial. The participating clinician further assesses eligibility, provides the potential participant’s parent/legal guardian with a verbal description of the trial and, if they are interested, provides a comprehensive Participant Information Sheet (PIS). All potential participants’ parents/legal guardians are given sufficient time to read the PIS, ask questions and consider participation before being asked to provide written informed consent if they are willing for their child to participate. Age-appropriate pictorial information sheets are also be provided for children who are old enough to use them.

Parents/legal guardians who consent to take part are asked to sign a consent form, which is also signed by the clinician who is taking consent. Parents/legal guardians are informed that they have the right to withdraw consent from participation in the OSTRICH trial at any time, and that the clinical care of their child is not affected at any time by declining to participate or withdrawing from the trial. Assent may be given by children who are able to understand the age-appropriate information provided and express an opinion regarding their participation.

All participating sites are asked to keep an anonymous screening log of all ineligible and eligible but not consented/not approached patients. These are used to measure potential selection bias.

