### Randomisation and blinding

#### Randomisation

Randomisation is coordinated centrally by the South East Wales Trials Unit (SEWTU). The randomisation schedule prepared by the Trial Statistician (TS) comprises random permuted blocks that are stratified by site and child’s age. The IMP Manufacturer (Piramal Healthcare UK Limited) was provided with a list of random allocation numbers linking to either the steroid or placebo. Whether the allocations relate to the steroid or placebo was determined by an independent statistician to ensure the TS remains blinded. The allocation numbers are used to label the trial medication packs. Each trial medication pack has a unique identification number (Trial Pack number).

As children are recruited, they are assigned the next vacant Participant Identification number (PID). Trial medication packs are only released once informed consent has been obtained and a consent form signed. Participants are randomised to receive either the steroid or the matching placebo by receiving the next sequentially numbered Trial Pack allocated to the participant by the site Pharmacy. A designated member of the OSTRICH trial site team (where possible) or the participant’s parent/legal guardian collects the pack from Pharmacy on behalf of the participant. Participant randomisation is considered to have occurred once a consent form is signed and the Trial Pack opened. The Trial Pack number is then entered onto the participant’s case report form (CRF).

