### Data collection

#### Baseline/clinical assessments

An eligibility case report form (CRF) is completed for all consented participants to ensure that they meet the eligibility criteria specified in the trial protocol. The clinician signs the form to confirm that the participant is eligible to be enrolled into the trial.

A participant registration form is completed by the OSTRICH nurse to register the participant and their parent/legal guardian to the trial (this includes collecting names and addresses of the participants and their parent/legal guardians).

The OSTRICH nurse and clinician complete the CRFs, recording medical history and audiometry, tympanometry and otoscopy measurements. Table 1 provides an explanation of the clinical assessments of this trial.

**Table 1 Tab1:** Clinical measurements

Measurement	Outcome
Audiometry	Hearing in each ear by pure tone audiometry, ear-specific insert visual reinforcement audiometry (VRA) or ear-specific play audiometry) or in both ears together by sound-field VRA or sound-field performance/play audiometry)
Tympanometry (using calibrated standardised tympanometers and modified Jerger classification Type B and C considered abnormal)	Presence of middle ear effusion in each ear
Otoscopy	Appearance of tympanic membrane

In current practice, the recommended standard methods to assess hearing thresholds are ear-specific pure tone audiometry (PTA) at 0.5, 1, 2 and 4 kHz in children 3 years or older, and sound-field visual reinforcement audiometry (VRA) in children under 3. However, equally, those children under 3 years of age may comply with PTA. Therefore, we recommend that the audiologist/clinician use their judgement on the most appropriate method of assessment for the child and, where possible, maintain that method for subsequent follow-ups.

We are aware that ear-specific VRA through the use of insert earphones is considered ‘gold standard’ practice but believe that sound-field VRA will provide a reasonable assessment of the child’s level of hearing and will ensure the feasibility and wider applicability of the trial in a range of research sites due to wider availability.

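### The primary logistic model adjusts for site only, leaving out age (a randomisation stratifier) and baseline hearing (recorded in every child): a modest loss of efficiency and consistency

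*Protocol article*

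**What the plan says.** Under Statistical analysis, the protocol article makes the primary analysis an intention-to-treat logistic regression of acceptable hearing at 5 weeks "between the two treatment arms, adjusting for site". No other covariate is named for it.

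Under Randomisation, the schedule uses "random permuted blocks that are stratified by site and child’s age". One stratifier is carried into the model and the other is not; no reason is given.

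Baseline hearing is available throughout:
- Inclusion criteria: "Audiometry confirming hearing loss of more than 20 dBHL averaged within the frequencies of 0.5, 1, 2, and 4 KHz in both ears", with a limit of 25 dBHL for sound-field testing.
- Registration and consent: "Each child has an audiometry assessment and a clinical assessment" before eligibility is judged.
- Baseline/clinical assessments: staff complete the CRFs, "recording medical history and audiometry, tympanometry and otoscopy measurements".

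Under Outcomes, the primary outcome is a cut at 20 dBHL (ear-specific) or 25 dBHL (sound-field) on that same average.

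Age appears once more in the analysis text, as a possible confounder entered with interaction terms for subgroup analyses that the article calls exploratory. Continuous secondary outcomes are to be adjusted for baseline. The full description of methods is left to a statistical analysis plan.

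**The concern.** An analysis normally carries the factors used to stratify the randomisation. Here the article names a covariate set that keeps only one of the two. An analysis plan that added age would depart from this text, so the matter is a stated choice and not a detail left open.

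Baseline hearing matters for a different reason. Every child starts on the wrong side of the threshold, but not at the same distance from it, and no upper limit on entry hearing loss is stated. Under the 20 dBHL rule, a child entering at 22 dBHL needs a 2 dB gain and one entering at 45 dBHL needs 25 dB. If entry level predicts 5-week hearing, a model without it uses the data less efficiently and does not correct for chance imbalance in starting severity. The measurement is already on the CRF, so using it needs no new data.

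**Working it through.** **1. The plan's own figure.** Inputs from Sample size: "from 20 % in the control group to 35 % in the intervention group", alpha 0.05, 80 % power; 1:1 allocation and a two-sided test are assumed.

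Uncorrected n per arm = [1.960·√(2·0.275·0.725) + 0.842·√(0.20·0.80 + 0.35·0.65)]² / 0.15² = (1.238 + 0.524)² / 0.0225 ≈ 138, or 276 in total. The continuity correction, n/4·[1 + √(1 + 4/(0.15·n))]², gives 151 per arm, or **302**, as stated. Allowing for 20 % loss, 302/0.8 = 377.5, so 378 against 380 stated. The figure reproduces.

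**2. Power as planned.** At 151 per arm without the correction, z = (0.15·√151 − 1.238)/0.622 = 0.97, giving 83.5 %. With all 380 analysed it is 91 %. Expected events at 302: 151·0.20 + 151·0.35 = 83.

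**3. Power with the covariates.** The article gives no prognostic strength, so a range is assumed. Simulation: 302 children, marginal rates held at 20 % and 35 %, Wald test at 1.96, 6,000 trials per setting. The latent 5-week hearing score has correlation ρ with baseline and an age effect of 0.3 SD, with treatment balanced within age group. Site was not simulated in this set. The Monte Carlo standard error is √(0.84·0.16/6000), about 0.5 points for each entry.

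| ρ | no covariate | + age | + age and baseline | gain from baseline over age |
|---|---|---|---|---|
| 0 | 84.2 % | 84.7 % | 84.7 % | 0.0 |
| 0.3 | 83.1 % | 83.6 % | 85.6 % | 1.9 |
| 0.5 | 83.9 % | 84.5 % | 89.7 % | 5.2 |
| 0.6 | 83.6 % | 84.0 % | 91.1 % | 7.1 |

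(Gains are taken before rounding.) Age alone adds 0.3 to 0.6 points at 0.3 SD, 1.2 at 0.6 SD and 2.8 at 1.0 SD.

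**4. The same question with site in the models**, since the protocol's model contains it. Assumptions: 10 sites, permuted blocks by site and age, 302 children, 1,500 trials per setting. Power for site only against site + age + baseline: 86 v 86 % (ρ = 0), 85 v 88 % (0.3), 85 v 92 % (0.5), 86 v 94 % (0.6). The gain survives adjustment for site. A separate set with 10 or 20 sites, 304 evaluable children and an age odds ratio of 2 put the gain from age at 0.2 to 0.7 points. In that set baseline added about 1 to 4 points at log odds ratios of −0.5 to −0.8 per SD.

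**5. Type I error.** In the step 3 simulation under the null (ρ = 0.5), it was 3.8 to 4.0 % with both variables omitted and 4.6 to 5.1 % with both included. With 10 sites in the model it was 4.5 to 5.2 %. With 20 assumed sites as fixed effects, one set gave 6 to 7.5 % in both the site-only and the fuller model, slightly more in the fuller one; another set with 10 or 20 sites showed no clear excess. Any such problem comes from many small sites and is already present in the site-only model.

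**6. Effect on the odds ratio.** The marginal odds ratio is (0.35/0.65)/(0.20/0.80) = 2.15. With a baseline log odds ratio of 0.75 per SD in absolute size, the conditional odds ratio that gives the same 20 % and 35 % is 2.33; at 1.0 per SD it is 2.47. The two answer slightly different questions.

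**The case against.** The case for leaving the model alone has real force.

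- **Age costs almost nothing in power.** This stands. Age is the only outright mismatch between design and analysis, and its case rests on matching the randomisation.
- **The gain from baseline rests on assumed inputs.** This stands. The 22 against 45 dBHL contrast shows why prediction is plausible, not how strong it is.
- **The trial is not short of power.** This stands. Every scenario without covariates exceeds 80 %, and the 20 % loss allowance is for 1 year whereas the primary outcome is at 5 weeks.
- **The contrast with the secondary outcomes is weak.** Largely accepted. Baseline adjustment is stated for continuous scores, which have the same score at entry. Every child fails the hearing threshold at entry, so the binary outcome has no baseline variation. The underlying dBHL value does vary, however, and could be used.
- **Detail is left to the analysis plan.** This disposes of any complaint that the absolute difference is not described as adjusted. It does not dispose of the covariate set, which the article itself names. The exploratory subgroup models do not put age into the primary comparison, and baseline hearing level is not named as a covariate for it.

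A reader might infer that the site-only analysis is invalid, biased or underpowered. The documents do not support that: allocation is randomised, the omission does not inflate type I error, and the sample size reproduces.

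**Conclusion.** The point holds as one of efficiency and consistency. The stated primary model drops one of two stratifiers and does not use an entry measurement, recorded in every child, of the quantity that defines the outcome.

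The size is modest: about 2 to 7 points of power from baseline hearing at 302 evaluable children for an assumed correlation of 0.3 to 0.6, nothing at zero, and usually under 1 point from age. I am confident of the direction and of what the text says, but less so of the magnitude, because no prognostic strength or number of sites is given. If baseline hearing proves uninformative, the simulations show no material loss from including it. It should be changed, but the trial's conclusions do not depend on it.

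**What to change.** Before unblinding, state the primary model as treatment + site + age stratum as randomised + baseline hearing level. Because ear-specific and sound-field results have different thresholds, enter baseline hearing in one of two ways:
- continuous mean dBHL (better ear or sound-field) with a term for test method; or
- distance above the applicable 20 or 25 dBHL threshold.

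Derive the absolute difference, with its 95 % confidence interval, from the same model by standardisation, next to the adjusted odds ratio. State how small sites will be pooled or otherwise handled if there are many. Keep the site-only model as a sensitivity analysis.

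The cost is a short addition to the analysis text and no new data. The conditional odds ratio changes slightly in meaning, which the standardised difference addresses. The model carries a few more parameters with about 83 expected events, which is a further reason to settle the handling of sites in advance.

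### Only the odds ratio is called adjusted, so the absolute difference on which the 15-point benefit is judged is not tied to the site-adjusted primary model (minor; clarify)

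*Protocol article*

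**What the plan says.** Three parts of the protocol article bear on this.

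- **Statistical analysis.** The primary analysis is a logistic regression comparing acceptable hearing at 5 weeks "between the two treatment arms, adjusting for site". The results follow in one sentence: "Comparisons will be presented as the absolute difference in proportions and the adjusted odds ratio", to be given with a 95 % interval and a P value. The word adjusted qualifies the odds ratio only. The sentence does not say how the difference is obtained, or whether the interval and P value belong to one measure or to both. The section closes by leaving the full description of methods to a statistical analysis plan, which is not shown.
- **Sample size.** The trial is planned to detect a change "from 20 % in the control group to 35 % in the intervention group", because "a 15 % absolute increase in the rate of resolution at 5 weeks would represent a clinically meaningful benefit". The benefit is thus defined on the absolute scale.
- **Randomisation.** The schedule uses "random permuted blocks that are stratified by site and child’s age".

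**The concern.** The figure that readers will set against the 15-point benefit is the absolute difference, and it is the one measure that the text does not link to the primary model. On the ordinary reading, a raw difference with an unstratified interval would stand beside an odds ratio and P value that allow for site.

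Two consequences could follow. If sites differ in their success rates, an interval that ignores site is wider than it need be. The interval for the difference and the adjusted P value could also fall on opposite sides of significance, and the text does not say which governs.

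The odds ratio cannot fill the gap. A site-adjusted odds ratio is conditional on site and non-collapsible, so applying it to the overall control rate does not return the overall absolute difference.

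**Working it through.** **1. The plan's own figure.** Inputs from Sample size: 20 % v 35 %, alpha 0.05 (taken as two-sided), 80 % power; 1:1 allocation is assumed.

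- Uncorrected n per arm = [1.960 × √(2 × 0.275 × 0.725) + 0.842 × √(0.20 × 0.80 + 0.35 × 0.65)]² / 0.15² = 137.9, so 138 per arm (276 in all).
- With continuity correction: (137.9/4) × [1 + √(1 + 4/(137.9 × 0.15))]² = 151 per arm, which is 302 as stated.
- 302/0.80 = 378, against 380 planned.

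The sample size stands.

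**2. Width of an unadjusted interval.** At 151 per arm the 95 % half-width is 1.96 × √[(0.16 + 0.2275)/151] = 9.9 points.

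**3. What adjustment for site can remove.** Let V0 and V1 be the between-site variances of the control and steroid success probabilities. In large samples the ratio of adjusted to unadjusted width is √[1 − (V0 + V1)/0.3875]. The article gives no between-site variation, so normal site effects on the logit scale are assumed, with overall rates held at 20 % and 35 %.

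- SD 0: V0 = V1 = 0; ratio 1.
- SD 0.4 (control success about 14 % to 26 % at ±1 SD): (0.0040 + 0.0078)/0.3875 = 0.030; ratio 0.985.
- SD 0.8 (about 9 % to 32 % at ±1 SD): (0.0147 + 0.0265)/0.3875 = 0.106; ratio 0.945.

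These are upper limits on the gain. With few sites, and site terms to estimate, the gain is a little smaller.

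**4. Simulation with 302 children.** Equal sites, 1:1 within site, 600 trials per setting. The unadjusted difference (unpooled interval, pooled z test) was compared with a site-adjusted difference (site fixed effects, robust standard error) and with the site-adjusted logistic Wald test. Half-widths are in points at 20 % v 35 %. Disagreement is unadjusted test v adjusted logistic test, over settings with and without an effect.

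| Site SD | Sites | Unadjusted | Adjusted | Ratio | Disagree at 0.05 |
|---|---|---|---|---|---|
| 0 | 10 / 20 | 9.9 / 9.9 | 9.9 / 9.9 | 0.997 / 0.995 | 0-1.7 % |
| 0.3 | 10 / 20 | 9.9 / 9.9 | 9.9 / 9.9 | 1.004 / 1.003 | 0.2-1.5 % |
| 0.5 | 10 / 20 | 9.8 / 9.9 | 9.7 / 9.7 | 1.017 / 1.016 | 0.5-3.0 % |
| 1.0 | 10 / 20 | 9.8 / 9.8 | 9.1 / 9.2 | 1.072 / 1.073 | 1.7-4.5 % |

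Coverage of the unadjusted interval was 93.5-97.2 % (Monte Carlo standard error about 0.9 points). The two point estimates differed by 0.05-0.5 points on average.

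**5. Simulation with 342 children** (380 × 0.90, assuming 10 % missing at week 5), 10 or 20 sites. The site-adjusted interval was 0-1 % wider at SD 0, under 1 % narrower at SD 0.4 and about 4 % narrower at SD 0.8. A site-stratified Mantel-Haenszel difference gave 1 % and 5 % narrower at SD 0.4 and 0.8. Verdicts differed in about 0.5-2 % of trials with the site-adjusted analysis.

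**6. Odds ratio against difference.** With overall rates fixed at 20 % and 35 % (true difference 15 points), the site-conditional odds ratio is (0.35/0.65)/(0.20/0.80) = 2.15 at SD 0, 2.23 at SD 0.5 and 2.47 at SD 1.0. Applied to a 20 % control rate (odds 0.25), these imply 0.25 × OR/(1 + 0.25 × OR) − 0.20 = 15.0, 15.8 and 18.2 points. The difference therefore needs a derivation of its own, averaging predictions over the children in the trial.

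**The case against.** The case against has four parts.

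- **The text never calls the difference crude.** This is true. A difference standardised from the site-adjusted model would fit the same sentence. A reader might infer that the plan commits to an unadjusted difference, but the document supports only the weaker statement that the difference is not said to be adjusted.
- **The method may be in the statistical analysis plan.** This also stands as a limit. If that plan already derives the difference from the primary model, only the article's wording is loose. What can be raised here is how a stated sentence attaches the word adjusted, not the absence of detail.
- **The harm is slight.** This stands. A reader might infer that the interval is too wide or that the primary result is compromised. Neither follows. The excess width is nil without site effects, and the article gives no figure for site variation. There is no bias. Some disagreement also comes from the logistic test itself: with no true effect it rejected in 4.5-7.7 % of trials, against 2.8-5.8 % for the unadjusted test.
- **The odds ratio does not fully reflect the design either.** This is correct. Randomisation is stratified by site and age, while the stated primary model adjusts for site only. Age appears later in the section, as a possible confounder for subgroup analyses.

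Giving an absolute and a relative measure together is good practice and is not criticised. What survives is that the headline absolute effect and the P value should rest on one analysis, and the sentence does not secure this.

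**Conclusion.** The point holds as a minor one. The measure on which benefit is defined is not tied to the site-adjusted primary model, although the trial randomises within site and age. If the difference is in fact unadjusted, its interval is wider by nothing without site effects, about 1 % at a site SD of 0.4 and about 4-5 % at 0.8. Its verdict differs from the adjusted test in about 0-5 % of simulated trials.

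These sizes rest on assumed site numbers (10 or 20), assumed site SDs, 1:1 allocation, and 302 or 342 evaluable children; the article gives neither the number of sites nor their variation. The sample size reproduces and the primary test is untouched.

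**What to change.** In Statistical analysis, state that the absolute difference and its 95 % confidence interval come from the primary logistic model by standardisation: the mean predicted probability with every child set to steroid, minus the mean with every child set to placebo, with a delta-method or bootstrap interval. Preferably add age, the other stratification factor, to that model. State which analysis the P value comes from. Present raw proportions per arm as description only.

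A site-stratified Mantel-Haenszel difference is an alternative, but it ties the two results less closely: in simulation its verdict still differed from the logistic test in 0.4-1.25 % of trials. Standardisation need not remove every borderline disagreement either, because the difference and the log odds ratio are tested on different scales; it does put both on one model.

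The cost is one or two sentences and standard software commands, with no new data and no more children. The change should be fixed before unblinding, so that no choice between two versions of the difference remains once results are known.
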